### Who will take informed consent? {26a}

Pregnant women will be recruited during ANC visits, regardless of their parity and the informed consent will be obtained by the MD of the study team on the field.

### Additional consent provisions for collection and use of participant data and biological specimens {26b}

It is mentioned in the informed consent form (ICF) that, in addition to the blood collected to perform tests in the field, blood spot will be collected for further examination.

### Interventions {6b}

#### Explanation for the choice of comparators

This study will compare the IPTp-SP strategy used in routine by the NMCP with the ISTp-US-Py to assess the non-inferiority of the second strategy for the prevention of maternal malaria, maternal anemia, spontaneous abortions or intrauterine death during pregnancy, fetal morbidity (premature birth, low birth weight, small for gestational age), and neonatal mortality at childbirth.

Pyramax® was the perfect drug to use for this procedure as it has been recognized by the NMCP as a drug that can be used during pregnancy in particular although the drug is not used in the overall population.

#### Intervention description {11a}

The ISTp-US-Py group will comprise pregnant women who will be screened monthly from the beginning of the 2nd trimester with us-RDT and who will be treated with Pyramax® if the test is positive.

Pyronaridine-artesunate (Pyramax®, Shin Poong Pharmaceutical Company, South Korea) is a film-coated tablet containing 180 mg of pyronaridine tetraphosphate and 60 mg of artesunate. As part of the EDCTP2 program supported by the European Union (RIA2017MC-2025-Pyrapreg), Shin Poong (Korea) agreed to donate us treatment for this study as well. The IPTp-SP group will be pregnant women who will receive SP as recommended by the National Malaria Control Program (NMCP) at weeks 16, 28, 32, and 36 of their pregnancy. SP (Fansidar®, Roche Laboratories, Switzerland) is a drug used for the treatment of uncomplicated malaria in children and adults and for IPTp. Fansidar is presented as scored tablets containing 500 mg of sulfadoxine and 25 mg of pyrimethamine. The drug continues to be beneficial to both mother and baby, even in areas of SP resistance [18].

#### Concomitant therapies

Any medication or other therapy taken by the study participant will be recorded.

#### Criteria for discontinuing or modifying allocated interventions {11b}

Changing the distribution of intervention is not possible in the framework of this study. In the event of an allergy or other adverse event (AE) that may impact participants’ health or that of the offspring, the participant will be removed from the study and will no longer receive the intended drug in the arm in which they were allocated.

#### Strategies to improve adherence to interventions {11c}

In order to ensure compliance with the protocol by the study personnel, two monitoring visits are planned throughout the study. The latter will focus on the review of source documents, the distribution of participants by study arm, and the accountability of the study drugs and tests.

#### Relevant concomitant care permitted or prohibited during the trial {11d}

It will be advised to the participants to return to the health center if they feel unwell to receive a concomitant therapy.

#### Provisions for post-trial care {30}

Coverage of care after the end of the study’s planned follow-up period is scheduled up to 28 days after delivery, though this is not a part of the study but rather for ethical reasons.

#### Outcomes {12}

##### Primary outcome

The primary outcome will be the assessment of the malaria status over the pregnancy at every visit for each study participant.

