### Objectives {7}

#### Main objective

The main objective of the study is to assess that the proportion of maternal malaria, maternal anemia, and their impact on the offspring is non-inferior when using ISTp-US-Py compared to IPTp-SP.

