## Methods: participants, interventions, and outcomes

### Study setting {9}

The study is carried out in DRC where malaria transmission is intense and perennial.

The study is conducted in the “Maternité Esengo,” a 106-bed health facility, located in Kisenso, Kinshasa, where there is an average of 100 deliveries per month. A previous study performed in a similar setting showed that the prevalence of malaria in pregnant women was 30% [4].

Pregnant women will be recruited during ANC visits, regardless of their parity.

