##### Physical and clinical examination

Vital signs (body temperature, pulse rate), blood pressure, and weight will be measured.

An obstetrical examination will be performed and the fetal viability will be recorded.PCR

Bloodspots of 50 μl will be collected on filter paper (Whatman grade 3) at each visit and subsequently every time a blood slide is done. Samples will be used to determine sub-microscopic parasitemia.Malaria diagnostic

In addition to an us-RDT detecting circulating *P. falciparum* antigens, thick and thin blood films will be prepared, dried, and stained with Giemsa according to standard operating procedures (SOP).

If positive, the parasite density (PD) will be calculated by counting the number of *P. falciparum* parasites per 200 leukocytes based on the actual number of WBC/μl. In case this information is missing, the PD will be estimated assuming WBC of 8000/μl. The PD per microliter will be calculated using the following formula:

$$\mathrm{Parasites}/\mathrm{\mu}\mathrm{l}(\mathrm P/\mathrm{\mu}\mathrm{l})=\frac{\mathrm{Number}\;\mathrm{of}\;\mathrm p\mathrm a\mathrm r\mathrm a\mathrm s\mathrm i\mathrm t\mathrm e\mathrm s\;\mathrm c\mathrm o\mathrm u\mathrm n\mathrm t\mathrm e\mathrm d\times8,000}{\mathrm N\mathrm u\mathrm m\mathrm b\mathrm e\mathrm r\;\mathrm o\mathrm f\;\mathrm l\mathrm e\mathrm u\mathrm k\mathrm o\mathrm c\mathrm y\mathrm t\mathrm e\mathrm s\;\mathrm c\mathrm o\mathrm u\mathrm n\mathrm t\mathrm e\mathrm d}$$

The thin smear will be examined for species determination.

Blood smears will be independently read by 2 qualified microscopists and the mean of the PD will be used in the study. Further details are described and explained in the SOP (SOP: quality control (QC) guidelines for the laboratories participating in the study).

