#### Study outcomes

##### Primary outcome

The primary outcome will be the assessment of asymptomatic/symptomatic malaria status and the parasite density of *P. falciparum* during pregnancy at every visit for every participant. The asymptomatic malaria status is defined as the presence of *P. falciparum* diagnosed by an us-RDT in the peripheral blood and a T°<37.5°C; symptomatic malaria is defined as the presence of *P. falciparum* diagnosed by an us-RDT in the peripheral blood and temperature and/or a history of temperature T°≥37.5°C. The parasite density is assessed by the quantification of *P. falciparum* parasites in the peripheral blood of participants by a thin blood smear examined by standard malaria microscopy.

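### The primary outcome is defined in incompatible ways, and its repeated results at every visit do not match the one yes/no proportion per woman that was sized

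*Protocol article*

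**What the plan says.** The protocol article describes the primary outcome in several places:

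- **Main objective:** to show that "the proportion of maternal malaria, maternal anemia, and their impact on the offspring is non-inferior" under ISTp-US-Py.
- **Outcomes {12}, Primary outcome:** "the assessment of the malaria status over the pregnancy at every visit for each study participant". Anemia, offspring outcomes and parasite density are not mentioned.
- **Statistical methods, Study outcomes, Primary outcome:** "the assessment of asymptomatic/symptomatic malaria status and the parasite density of" P. falciparum, again at each visit in pregnancy. Positivity is by us-RDT in peripheral blood.
- **Secondary objectives:** malaria proportions (asymptomatic/symptomatic) and parasite densities during pregnancy appear here, with anemia and offspring outcomes.

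Sample size {14} uses a calculator for a binary non-inferiority outcome, with a 10% difference, 5% significance and 80% power. Table 2 gives totals of 122 (low birth weight), 196 (malaria, 18.9% vs 23.4%) and 220 (anemia). Recruitment {15} takes 220 and inflates it to 242.

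Table 1 has two maternal blocks. The first marks malaria tests from time 0 to M6, the second from M1 to delivery. Both interventions are marked from M1 to M6.

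The statistical section defines asymptomatic malaria as a positive test with temperature below 37.5°C. Symptomatic malaria is a positive test with "temperature and/or a history of temperature T°≥37.5°C". Density is to come from a thin smear. Physical and clinical examination counts parasites per 200 leukocytes and adds: "The thin smear will be examined for species determination".

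**The concern.** A non-inferiority verdict needs one variable, one summary per woman and one time window. Here the sections disagree on the variable itself. Women and study staff know the allocation, so a protocol that supports several primary comparisons leaves room for dispute over which one carries the verdict.

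The unit also differs: the outcome is a series of visit results, while the sizing is for one proportion of women. An ever-positive proportion and a per-visit proportion are different quantities, and the same 10-point margin does not mean the same thing on both.

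The window is open at the start. Infections present before any intervention are balanced by randomisation. Counting them would pull a real difference towards zero, which in a non-inferiority trial favours the new strategy when it is truly worse.

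**Working it through.** **1. The sections side by side**

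| Section | Malaria status | Density | Anemia, offspring |
|---|---|---|---|
| Main objective | main | not named | main |
| Outcomes {12} | primary | not named | secondary |
| Study outcomes | primary | primary | secondary |
| Secondary objectives | secondary | secondary | secondary |

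No two rows agree. The total of 220 comes from the anemia row, which both outcome sections treat as secondary.

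**2. The plan's own sample size**

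n per arm = (z0.95 + z0.80)² × [p1(1−p1) + p2(1−p2)] / D², with (1.645 + 0.842)² = 6.18.

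- Malaria: 0.189×0.811 + 0.234×0.766 = 0.3325; D = 0.10 + 0.045 = 0.145; n = 6.18×0.3325/0.0210 = 97.8, so 98 per arm and 196 in total, as stated.
- Anemia: 0.30×0.70 + 0.25×0.75 = 0.3975; D = 0.10 + 0.05 = 0.15; n = 6.18×0.3975/0.0225 = 109.2, so 110 per arm and 220 in total, as stated.
- Low birth weight gives 122 in the same way.

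The figures reproduce exactly with one yes/no result per participant and a one-sided 5% level. The sizing is therefore per woman, although the outcome is written per visit. (The malaria row reproduces only if infection rates are entered as success rates. That is a separate matter.)

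**3. What counting pre-intervention tests would do**

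Inputs: 18.9% in the IPTp-SP arm (Table 2); 28.9% in the ISTp arm, a true difference equal to the margin; 110 per arm; baseline prevalence b = 30%. This b is an assumption, taken from Study setting {9}, where a study in a similar setting "showed that the prevalence of malaria in pregnant women was 30" per cent. Later infection is assumed independent of baseline infection.

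Ever-positive rate = b + (1−b)p:

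- IPTp-SP: 0.30 + 0.70×0.189 = 43.2%
- ISTp: 0.30 + 0.70×0.289 = 50.2%
- Apparent difference: 0.70×10 = 7.0 points

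SE = √[(0.432×0.568 + 0.502×0.498)/110] = 6.71 points. Chance that the upper limit falls below 10 points:

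- Two-sided 95% interval: Φ((10−7.0)/6.71 − 1.96) = Φ(−1.51) = 6.5%, against 2.5% nominal.
- One-sided 5%: Φ((10−7.0)/6.71 − 1.645) = Φ(−1.20) = 11.5%, against 5% nominal.

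For b from 10% to 40%, the apparent difference runs from 9.0 to 6.0 points and the two error rates from 3.6% to 8.6% and from 6.9% to 14.7%.

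For a per-visit proportion with one of seven tests before intervention, 10 points becomes 10×6/7 = 8.6. By simulation with woman-level variance, the 2.5% error becomes about 7–9%. If the M1 test, taken before the first treatment, also counts, the difference is 10×5/7 = 7.1 points and the error about 16–25%.

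**4. The same check at the planning rates**

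With 18.9% vs 23.4% and b = 30%, the difference falls from 4.5 to 0.70×4.5 = 3.2 points. The chance of declaring non-inferiority (one-sided 5%, 110 per arm) hardly moves, from 26% to 27%, because the variance rises too. With no true difference the estimate is not shifted.

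**5. The definitions**

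A woman who tests positive, is below 37.5°C at the visit and reports an earlier fever meets both symptom definitions. For density, a thin smear is named in one section, while the other assigns the thin smear to species and does not say which film is counted.

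**The case against.** The strongest reply is that much of this belongs in an analysis plan. Data management and storage promises a pre-established one, to be submitted to the Trial Steering Committee, and the statistician is to be blinded. Which visits count, how they are combined and how correlation is handled are commonly settled there. That stands for the details. It does not cover the contradiction: any analysis plan would have to overrule at least one section of the protocol.

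A reader might infer that the protocol counts the time-0 test and so is biased towards non-inferiority. The documents do not say so. General analysis principles speaks of baseline and at least one further visit, which can be read either way. Baseline data are summarised separately, and the second maternal block of Table 1 starts at M1. The bias is therefore conditional, and it arises only when ISTp is truly worse.

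A reader might also infer that the confidence interval will be too narrow. With six visits and an assumed within-woman correlation of 0.3, the design effect is 1 + 5×0.3 = 2.5, and an interval ignoring it would cover about 79%. But no section plans to treat visits as independent. Likewise, nothing says that 18.9% and 23.4% are per-visit rates. If they were, six independent visits would give 1 − 0.811⁶ = 71.5% vs 1 − 0.766⁶ = 79.8% ever positive, a gap of 8.3 points. Both figures are illustrations only.

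The symptom overlap cannot change whether a woman is us-RDT positive, and the film question touches density alone. Both are minor beside the main point.

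**Conclusion.** The point holds as a contradiction in the protocol. The primary variable differs between sections, and the repeated-visit outcome does not match the per-woman proportion that was sized. This needs no assumption.

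The effect of pre-intervention tests is a conditional risk that the text leaves open. If they counted in an ever-positive outcome, a true 10-point inferiority would show as 7.0 points, with false non-inferiority of 6.5% instead of 2.5%, or 11.5% instead of 5%. This rests on 30% baseline prevalence, independence of later infection, true inferiority exactly at the margin and 110 women per arm. The overlapping symptom classes and the unclear film for density are real but secondary.

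**What to change.** Before database lock, name one primary variable in the same words in Main objective, Secondary objectives, Outcomes {12} and Study outcomes: per woman, any us-RDT-positive P. falciparum result (yes/no) at any scheduled or unscheduled visit after the first intervention visit. State whether the window ends at the last pregnancy visit or at delivery. Unscheduled visits belong in it, because women who feel unwell are asked to return and are tested then. Analyse it as a risk difference against the 10-point margin.

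Make parasite density, anemia and offspring outcomes secondary. Any per-visit analysis should account for correlation within a woman. Baseline covariates are optional.

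State that the Table 2 malaria rates are assumed to apply to this per-woman variable. Define asymptomatic as positive, below 37.5°C and without a history of fever. Reconcile Physical and clinical examination with Study outcomes on which film gives the density; the documents do not settle it.

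The cost is wording. The tests are already scheduled, recruitment is complete, and the article was submitted before the last visit. Somewhat fewer events will be counted. The Table 2 rates may also not fit the chosen variable. In the illustrative case of 71.5% vs 79.8%, the SE at 110 per arm is 5.8 points and the chance of showing non-inferiority only about 5% (two-sided 95% interval) to 9% (one-sided 5%). The rewording makes the comparison unique; it does not show that the sample is large enough.

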##### Secondary outcomes

During pregnancy, the following outcomes will be assessed at every visit for each study participant: the anemia status, the incidence of spontaneous abortions, and the intrauterine deaths.

At birth, the outcomes will be assessed as follows in the offspring: the fetal morbidity and the intrauterine death.

Within the 28 days of post-partum, the following outcomes will be assessed in the infant: the early neonatal mortality and the neonatal mortality.

### Participant timeline {13}

Pregnant women fulfilling the inclusion/exclusion criteria will be recruited during the ANC visit over an enrollment period of about 20 months. At every scheduled and unscheduled visit, the study team will collect vital signs, blood pressure, weight, data on the medical history since the last visit (including any treatment taken), information on any AE, and current signs and symptoms (if any). At the same time, the team will collect blood samples for malaria diagnosis (us-RDT, thick and thin blood film), Hb, and dried blood spots.

The outcome of pregnancy, birth weight, APGAR score, and maternal Hb will be collected as soon as possible after delivery. A placental blood sample will be collected for the diagnosis of malaria (thin blood film) and dried blood spots. The newborn will be examined for congenital abnormalities and will be reassessed again at day 28 (Table 1).

**Table 1 Tab1:** Time and event schedule

	Enrolment	Allocation								
Timepoint**	-t_**1**_	0	M_**1**_	M_**2**_	M_**3**_	M_**4**_	M_**5**_	M_**6**_	Delivery	4–6 weeks post-end of pregnancy

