#### Procedure for unblinding if needed {17b}

Not applicable. The study team and the participants themselves will all be aware of the arms where participants will be included.

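### As written, the primary malaria outcome takes in tests from unscheduled visits that unblinded women start themselves, so unequal attendance can bias the comparison in either direction.

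*Protocol article*

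**What the plan says.** Under Outcomes {12}, the protocol article states: "The primary outcome will be the assessment of the malaria status over the pregnancy at every visit for each study participant". The Primary outcome paragraph in the statistics section repeats the scope as "during pregnancy at every visit for every participant". There a positive us-RDT is the defining event, with or without fever; the asymptomatic case, for example, is infection "diagnosed by an us-RDT in the peripheral blood and a T°<37.5°C".

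The testing rule is in Participant timeline {13} and again in Plans for assessment and collection of outcomes {18a}: "At every scheduled and unscheduled visit, the study team will collect vital signs", and on the same occasion "the team will collect blood samples for malaria diagnosis (us-RDT, thick and thin blood film"). Table 1 lists monthly visits M1 to M6 and delivery. It does not say that tests taken at other times are left out of the outcome.

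Unscheduled visits begin with the woman. Section {11d} advises participants "to return to the health center if they feel unwell". The trial is open label: "The study team and the participants themselves will all be aware of the arms" (section {17b}). Only the statistician is blinded (section {17a}).

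**The concern.** Read together, these sections combine two kinds of testing in one outcome. One follows a fixed monthly schedule meant to be the same in both arms. The other depends on when a woman chooses to attend. One arm receives a preventive drug, the other a monthly test with treatment only if it is positive, and every woman knows which she has. Willingness to come in between appointments may therefore differ by arm even if infection does not.

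The us-RDT being objective does not help, because the bias lies in how often a woman is tested. Blinding the statistician and analysing by intention to treat do not address it either. If IPTp-SP women make more unscheduled visits, more of their infections are found and ISTp-US-Py looks better, which favours a non-inferiority claim. If ISTp-US-Py women attend more, the bias runs against them and power falls.

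**Working it through.** **Inputs from the article.** Margin 10 points, significance level 5%, power 80% (Sample size {14}); malaria 18.9% under IPTp and 23.4% under IST, stated total 196 (Table 2); minimum total 220, that is 110 per arm (Recruitment {15}); two-sided 95% intervals (General analysis principles); six monthly visits (Table 1).

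**Inputs assumed.** The extra unscheduled tests per woman in one arm (*e*), the positivity of those tests (*p*) and the per-woman summary are not given. The 30% in Study setting {9} is a prevalence among pregnant women in a similar setting. It serves here only as an upper guide to *p*.

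**The plan's own figure.** With one-sided 5%, (1.645 + 0.842)² × (0.189 × 0.811 + 0.234 × 0.766) / (0.10 + 0.045)² = 97.8, so 98 per arm and 196 in total. The stated figure reproduces, and it treats malaria as one binary result per woman. (It does so only with the 4.5-point excess added to the margin rather than subtracted. That is a separate matter and is not used below.)

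**Ever-positive summary.** With true infection equal in both arms and a base of 18.9%, shift = (1 − 0.189) × (1 − (1 − *p*)^*e*):

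| *e* | *p* = 10% | *p* = 30% |
|---|---|---|
| 0.10 | 0.8 points | 2.8 points |
| 0.25 | 2.1 points | 6.9 points |

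This assumes that none of the extra infections would have been found at the next monthly test. If half would have been, the range of 0.8 to 6.9 becomes about 0.4 to 3.5 points.

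**A lower positivity.** If 18.9% is the ever-positive rate over six independent monthly tests, positivity per test is 1 − 0.811^(1/6) = 3.4%. If unscheduled tests were no more often positive than that, *e* = 0.25 would add 0.7 points.

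**Share-of-positive-tests summary.** Share = (6 × *ps* + *u* × *pu*) / (6 + *u*), where *ps* and *pu* are positivity at scheduled and unscheduled tests and *u* is unscheduled tests per woman. With *u* = 0.25 in one arm and 0 in the other:
- *ps* = 5%, *pu* = 40%: (0.30 + 0.10) / 6.25 = 6.4%, a shift of 1.4 points.
- *ps* = 18.9%, *pu* = 20%: (1.134 + 0.05) / 6.25 = 18.94%, a shift of 0.04 points.

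**Effect on the conclusion.** Normal approximation, 110 per arm. False non-inferiority takes true rates of 28.9% and 18.9%, with the control rate inflated by the shift. Power takes 18.9% in both arms, with the ISTp rate inflated by the shift.

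| Shift (points) | False non-inferiority, one-sided 5% | False non-inferiority, two-sided 95% CI | Power, one-sided 5% | Power, two-sided 95% CI |
|---|---|---|---|---|
| 0 | 5.0% | 2.5% | 60% | 47% |
| 2 | 9.7% | 5.3% | 44% | 32% |
| 3 | 12.9% | 7.4% | 36% | 25% |
| 5 | 21.1% | 13.2% | 23% | 15% |

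If only scheduled tests count, unequal unscheduled attendance shifts the tested difference by 0, apart from its indirect effect when an infection is found and treated between visits.

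**The case against.** The strongest reply is that no sentence says outright that unscheduled tests enter the primary outcome. The passages on unscheduled visits are data-collection rules that also cover vital signs and adverse events. Visits are described as monthly, Table 1 lists only those and delivery, and a data analysis plan is promised. Part of this stands: a reader could take every visit to mean every visit in Table 1. But the text names unscheduled visits, takes the defining test at them, and scores malaria at every visit without limit. The point rests on what is stated, not on detail left to an analysis plan.

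A second reply is that the size depends on chosen inputs. This stands. A reader might infer that attendance alone will move the difference by several points, or that the bias favours non-inferiority. The documents support neither: they give no attendance gap and no unscheduled positivity, and the direction could be either.

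A third reply is that extra unscheduled visits may reflect extra clinical malaria, which the primary outcome expressly includes. This also stands. A reader might infer that unscheduled positives should leave the primary outcome. That would remove illness arising between screens, where a screening strategy could fail, and could itself favour non-inferiority. Scheduled visits can also be missed unequally.

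**Conclusion.** The point holds in conditional form. As written, the primary outcome lets attendance that may depend on the arm change a woman's chance of being scored positive, and nothing in the article prevents this. Under an ever-positive summary, with 0.1 to 0.25 extra tests per woman and 10–30% positivity, the shift is roughly 1 to 7 points of a 10-point margin. It is about half that if half of the infections would surface at the next monthly test, below 1 point if unscheduled positivity is as low as 3.4%, and about 0 to 1.4 points for a share of positive tests. The ever-positive reading fits the sample size best, but the article does not fix it. A 3-point shift would be enough to raise false non-inferiority from 5% to about 13% at one-sided 5%, or to cut power from 60% to 36% in the other direction. These are illustrations of what is at risk, not estimates of a bias that has occurred.

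**What to change.** In both Primary outcome paragraphs (Outcomes {12} and the statistics section), state which visits count. Then, before the arms are compared:

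- Prespecify, beside the all-visits analysis, a non-inferiority analysis limited to tests scheduled in both arms (the monthly visits of Table 1 and delivery).
- Report symptomatic malaria at unscheduled visits separately, as events per woman-month by arm, so that it is not lost.
- Tabulate scheduled and unscheduled tests per woman by arm.
- Treat a non-inferiority conclusion as robust only if the two analyses are consistent.

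The restricted analysis needs the same test schedule in both arms. Table 1 shows monthly visits for both, while Intervention description {11a} lists four gestational weeks for the comparator, so these passages should be reconciled as far as testing occasions are concerned.

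The cost is some wording, one extra analysis of data already collected, and a somewhat more cautious conclusion if the two results differ. The article says that analysis follows the last participant's follow-up, and it was submitted before the last visit, so on its own timetable the rule could still be fixed in advance.
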